### Sample Size

We will use a 2 × 2 factorial design for this MOST trial (detailed in the Intervention Design subsection). Our sample size and power calculations for the primary outcome (health-related quality of life) assume an overall 2-sided type I error rate of 5%, 80% power, and an analysis of covariance–based approach with 2 independent dichotomous factors (ie, each factor has 2 levels). We will assume an attrition rate of 20%, with 160 (80%) participants completing the study (referred to as completers) from 200 participants enrolled. Under these assumptions, we will have 80% power to detect at least a minimally detectable difference (Cohen *d*) of 0.36 for the main effect or 0.18 in terms of the standardized regression coefficient. In these calculations, we assume a conservative correlation of 0.6 between the baseline covariate and outcome, which is similar to that in a previous study by Froehlich-Grobe et al [4]. In addition, 12 participants will be enrolled for pilot-testing the My Health, My Life, My Way program [28].

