### Statistical Methods

All statistical analyses will be conducted in an intent-to-treat manner at the individual level taking into account the correlated nature of data (multiple time points for every participant). Statistical significance will be evaluated at a type I error rate of 5%. Quality control will include descriptive and graphical approaches to summarize baseline characteristics of all key variables. With respect to data, we will begin by systematically cleaning and verifying all collected data, as well as examining ranges, missing values, and provenance. The significance tests conducted for the primary outcome are all specified a priori and modest in number. Consistent with published guidelines for statistical reporting, exact *P* values (rather than, eg, “*P*<.05” or “NS” [not significant]) will be reported [39]. This allows readers who may have their own opinions about multiple testing corrections, configurations of a family of hypotheses, and costs of type I errors to set the significance level to know the raw, uncorrected result and make their own judgments about statistical significance [40,41]. As Saville [42] noted, in multiple comparison issues, there is no right answer, and each investigator must ultimately “cut the Gordian knot” themselves. To evaluate the potential systematic variation among the study arms, key variables such as age, race, sex, disability type, and physical function at baseline will be examined and compared for relationships with study arms. If a potential confounder is found to differ meaningfully among the groups and if we find that the inclusion of the covariate improves the corrected Akaike information criterion (AIC), it will be included as a covariate in our analyses. We will estimate and test the effects of the 4 individual intervention components by means of a full factorial experiment. First, we will fit a linear mixed model to account for correlated data, to check whether each factor has a significant effect on outcome change across the time points (baseline and 6 months). For each of the 2 components, we will determine whether there is a difference in change across time using baseline as the reference cell (ie, 6 months vs baseline). This would be considered the main effect of each component on the pre-post difference. However, statistically, these effects will be modeled as component-by-time interactions, with the 6-month outcome as the primary end point. We will also include interactions among the components (eg, factor 1 × factor 2 × time interaction). In terms of multiple testing, given that this is a pilot project (ie, an exploratory and not confirmatory trial), we will estimate the false discovery rate and false discovery proportion based on the *P* values for all outcomes.

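### Entered as a main effect, a covariate picked by the imbalance-and-AICc rule leaves the component-by-time effect unchanged with complete data and barely corrects it under random dropout

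*Protocol article*

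**What the plan says.** Three statements in the Protocol article have to be read together.

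- **Selection rule (Statistical Methods).** The candidates are named: "key variables such as age, race, sex, disability type, and physical function at baseline will be examined". The rule has two conditions: the variable is unbalanced across arms, and its inclusion "improves the corrected Akaike information criterion (AIC), it will be included as a covariate in our analyses".
- **Target of the primary analysis (Statistical Methods).** A linear mixed model is fitted to "check whether each factor has a significant effect on outcome change across the time points (baseline and 6 months"), so the baseline score is a response. The text then says that "these effects will be modeled as component-by-time interactions, with the 6-month outcome as the primary end point". It also adds the two-component interaction with time.
- **Sample size (Sample Size).** The calculations "assume an overall 2-sided type I error rate of 5%, 80% power, and an analysis of covariance–based approach", with a baseline-to-outcome correlation of 0.6, 200 enrolled and 160 completers.

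Time interactions are named for the components and for their joint effect. None is named for an adjustment covariate.

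**The concern.** The tested quantity is a difference in change from baseline to 6 months. Age at entry, race, sex and disability type are fixed over that period. Entered as a main effect, such a variable moves both scores by the same amount, so it drops out of the change.

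An imbalance that only affects the level of quality of life is already removed by differencing. An imbalance that matters here is one in a variable that predicts change, and that is the kind a main effect does not reach. The coaching or reward effect could then be reported as adjusted for a noted imbalance while that imbalance is still in the estimate. AICc judges the fit of the whole model, so it can favor a covariate that has no bearing on the tested contrast.

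Baseline physical function, where it is the baseline value of the outcome itself, is a separate matter and is not part of this point.

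**Working it through.** **1. The plan's own figure.** Inputs from Sample Size: two-sided 5%, 80% power, 160 completers, r = 0.6. For one factor under ANCOVA, d = (1.960 + 0.842) × 2 × √(1 − 0.6²) / √160 = 0.354 (0.357 with the t distribution). Half of this is 0.177 to 0.178. The stated 0.36 and 0.18 reproduce, and 160 / 0.8 = 200. The sample size therefore rests on a model in which an added covariate does adjust the 6-month effect.

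**2. Algebra for the stated mixed model.** Let A be a component and x a time-fixed covariate:

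- y0 = a0 + c0·A + b·x + error
- y6 = a6 + c6·A + b·x + error
- D = y6 − y0 = (a6 − a0) + (c6 − c0)·A + error, with no x

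Define S = y0 + k·D with k = −Cov(y0, D)/Var(D), so that S and D are uncorrelated. S contains b·x. Its intercept and its coefficient on A are free because c0 is free, so S carries no information on c6 − c0. With complete data the component-by-time estimate thus comes from D alone and is identical with or without x, for any within-person covariance. This step needs no assumed sizes.

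**3. AICc.** Assume residual SD 1, within-person correlation 0.6, a covariate slope of 0.5 on both scores and none on change. With equal variances S = (y0 + y6)/2, with residual variance 0.6 + 0.4/2 = 0.8. Adding x lowers −2 log-likelihood by about 200 × ln((0.8 + 0.25)/0.8) = 54. After a penalty of about 2, AICc improves by about 52 points while the tested estimate does not move.

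**4. Simulation of size.** Assumed, not from the protocol: the same residual structure; 200 participants; imbalance of 0.4 SD between levels of one factor; slope 0.5 at both times; an extra slope on change of 0 or 0.4; true component effect 0.36. There were 150 REML fits per setting, so means carry Monte Carlo error of about 0.139/√150 = 0.011. CS is compound symmetry, UN is unstructured.

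| Setting | Slope on change | No covariate | Main effect | With covariate × time |
|---|---|---|---|---|
| Complete, CS | 0.4 | 0.513 (SE 0.139) | 0.513 (SE 0.139) | 0.352 (SE 0.129) |
| Complete, UN | 0.4 | 0.526 | 0.526 | 0.369 |
| 20% random dropout, CS | 0.4 | 0.548 | 0.545 | 0.379 |
| 20% random dropout, UN | 0.4 | 0.512 | 0.513 | 0.351 |
| About 22% dropout by covariate and arm, CS | 0 | 0.316 | 0.368 | 0.370 |
| About 22% dropout by covariate and arm, CS | 0.4 | 0.335 | 0.408 | 0.353 |
| Complete, UN, baseline means set equal | 0 | 0.428 | 0.364 | 0.362 |
| Complete, UN, baseline means set equal | 0.4 | 0.546 | 0.479 | 0.353 |

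The bias expected from the inputs is 0.4 × 0.4 = 0.16. With complete data and free baseline means the main effect changed no estimate in any replicate. With random dropout it moved single estimates by 0.010 to 0.019 on average, and the mean bias stayed.

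**5. How likely such an imbalance is.** With 100 per factor level, the standard error of a standardized covariate difference is 2/√200 = 0.141. An imbalance of 0.3 SD is 2.1 standard errors and 0.4 SD is 2.8. At a slope of 0.3, a 0.3 SD imbalance leaves 0.09 SD; a one-standard-error imbalance leaves 0.141 × 0.3 = 0.04 SD.

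**The case against.** The strongest reply is that the protocol never says main effect only. The form of a covariate is a detail that a condensed article may leave to the full plan, and the ANCOVA language under Sample Size suggests a model in which the covariate would work. The first part stands: the main-effect form is a reading. It is the natural one, because the same paragraph spells out time interactions wherever it wants them. The protocol also does more than stay silent. It states a selection rule and a target parameter, and on that reading the two do not fit each other or the ANCOVA basis of the sample size.

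A reader might infer that the covariate can never change the result, so that no adjustment takes place at all. The documents do not support that. They plan for 20% attrition and keep incomplete participants in the likelihood under missing at random. Those participants let the covariate act, and when dropout depends on covariate and arm the estimate moves by about 0.05 to 0.07. That move can help (0.316 to 0.368) or overshoot (0.335 to 0.408, true value 0.36). If baseline means were constrained equal, the main effect would act even with complete data, though it would not remove bias through change (0.479). The protocol states no such constraint. The rule also covers outcomes such as usability, which have no baseline measurement and hence no change contrast.

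It also stands that the sizes are assumed, that imbalances this large are uncommon, that randomization keeps the unadjusted contrast unbiased on average, and that the trial describes itself as exploratory. AICc need not always select such a term; that depends on how strongly the covariate predicts level.

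**Conclusion.** The point holds in a limited form. Read naturally, the rule puts a time-fixed covariate into the model as a main effect. With complete data and unconstrained baseline means this leaves each component-by-time estimate exactly unchanged. With random dropout near the planned rate, an imbalance that predicts change remains almost fully in the estimate. Dropout related to covariate and arm gives the covariate more influence, not reliably in the right direction. A better AICc is no evidence that the component effect has been adjusted.

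The exact cancellation rests on algebra alone. The size of any remaining bias is imbalance times slope on change: 0.04 to 0.09 SD in the milder assumed cases and 0.16 in the harsher one, against a detectable difference of 0.36. The protocol supplies neither factor. The matter deserves correction because the rule exists for exactly the case of a chance imbalance, and on this reading it would not deal with it.

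**What to change.** Choose one of the following and state it in Statistical Methods:

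- **Preferred:** model the 6-month score with the baseline score, the two components, their interaction and the adjustment covariates as regressors. This agrees with the ANCOVA basis of the sample size. Participants without a 6-month score can be handled by the multiple imputation the protocol already lists.
- **If baseline stays a response in the mixed model:** enter each adjustment covariate with both its main effect and its covariate-by-time term.

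These are different estimators. At r = 0.6 and unit variance, the residual variance is 1 − 0.36 = 0.64 for ANCOVA and 2 × (1 − 0.6) = 0.80 for change with free baseline means, so ANCOVA is the more precise.

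In either case, do not treat an improvement in whole-model AICc as showing that the component effect has been adjusted.

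The cost is a sentence or two of text and at least one degree of freedom per covariate, more for multi-category variables such as disability type and race. Where a covariate does not predict change, its time term slightly widens the standard error (0.126 to 0.129 in the complete-data simulation). No new data are needed.

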### Study Survey Packets

After enrolling in the study, participants will automatically be electronically delivered a REDCap link to a survey packet. This survey packet will include demographics and outcome measures (Table 2). Participants will be asked to complete this survey packet 3 times during the 6-month study period (excluding the demographics in the first survey packet). The surveys should take approximately 20 minutes to complete at each time point. The time points include baseline, 3 months, and 6 months.

**Table 2 table2:** Measures of effectiveness.

Variables^a^	Instruments	Time points
Health-related quality of life	Enabled version of 36-item Short Form Health Survey (primary outcome)	Baseline, 3 months, and 6 months
Physical activity	Godin Leisure-Time Exercise Questionnaire	Baseline, 3 months, and 6 months
Physical activity	Minutes, steps, and related data from Fitbit	Continuous
SE^b^ for managing symptoms	PROMIS^c^ Item Bank v1.0–Self-Efficacy for Managing Chronic Conditions–Managing Symptoms–Short Form 4a	Baseline, 3 months, and 6 months
SE for managing daily activities	PROMIS Item Bank v1.0–Self-Efficacy for Chronic Conditions–Managing Daily Activities–Short Form 4a	Baseline, 3 months, and 6 months
SE for managing sleep disturbance	PROMIS Item Bank v1.0–Sleep Disturbance–Short Form 4a	Baseline, 3 months, and 6 months
Psychosocial Illness	PROMIS Item Bank v1.0–Psychosocial Illness Impact-Positive–Short Form 8a	Baseline, 3 months, and 6 months
SE for managing emotions	PROMIS Item Bank v1.0–Self-Efficacy for Managing Chronic Conditions–Managing Emotions–Short Form 4a	Baseline, 3 months, and 6 months
SE for managing social interactions	PROMIS Item Bank v1.0–Self-Efficacy for Managing Chronic Conditions–Managing Social Interactions–Short Form 4a	Baseline, 3 months, and 6 months
Emotional distress	PROMIS Item Bank v1.0–Emotional Distress-Depression–Short Form 4a	Baseline, 3 months, and 6 months
SE for managing medications and treatments	PROMIS Item Bank v1.0–Self-Efficacy for Managing Chronic Conditions–Managing Medication and Treatment–Short Form 4a	Baseline, 3 months, and 6 months
SE for managing sleep-related impairments	PROMIS Short Form v1.0–Sleep-Related Impairment–Short Form 4a	Baseline, 3 months, and 6 months
Dietary intake	Short Healthy Eating Index	Baseline, 3 months, and 6 months
Medication adherence	Medication Adherence Rating Scale and Beliefs About Medication Questionnaire	Baseline, 3 months, and 6 months

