
Our 3-pronged approach involves minimizing missing data, leveraging the maximum likelihood–based approach or the multiple imputation approach under the assumptions of ignorability (ie, missing-at-random [MAR] assumption), and conducting multiple sensitivity analyses assuming MAR as well as missing not at random [43,44]. Analytically, our choice of mixed models to account for the repeated nature of the data will allow us to handle missing data for the primary and secondary outcomes under the assumptions of MAR. The MAR mechanism is ignorable when mild regularity conditions are satisfied. Such inferences can proceed by analyzing the observed data only, without explicitly addressing a form of the MAR mechanism. Missing data in other independent variables (mediators or other covariates) will be handled through the expectation-maximization algorithm coupled with bootstrapping for SEs, which will give maximum likelihood–based imputation under the MAR assumption [43].

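### The primary mixed model is described with baseline and 6 months only, and the planned 3-month SF-36E score has no stated role in it or in the missing-data analyses

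*Protocol article*

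**What the plan says.** **Data collection.** Study Survey Packets sets three survey occasions: "The time points include baseline, 3 months, and 6 months". Table 2 and the Outcome Measures section confirm that SF-36E, the primary outcome, is taken at all three.

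**Primary model.** Statistical Methods fits a linear mixed model "to check whether each factor has a significant effect on outcome change across the time points (baseline and 6 months". The sentences that follow describe the contrast as 6 months against baseline, call the effect a pre-post difference, and model it as a component-by-time interaction with the 6-month outcome as the primary end point. The 3-month visit is not named.

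**Missing data.** The second part of Statistical Methods says that "our choice of mixed models to account for the repeated nature of the data will allow us to handle missing data" under missing at random. It also offers multiple imputation as an alternative to likelihood, and sensitivity analyses under missing at random and missing not at random. It does not say which variables or visits enter any of these.

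**Sample size.** "We will assume an attrition rate of 20%, with 160 (80%) participants completing the study". The calculation is a baseline-adjusted comparison at one follow-up time ("assume an overall 2-sided type I error rate of 5%, 80% power, and an analysis of covariance–based approach").

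**The concern.** A mixed model handles dropout through what it observes on each person before they leave. With two occasions there is nothing between baseline and the end point. Someone who answers at 3 months and then leaves looks the same to the model as someone who left in week 1. The missing-at-random assumption then requires that dropout, given baseline score and factor levels, is unrelated to how the participant was doing at 3 months. Adding the 3-month score weakens that requirement for everyone who leaves after it.

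The matter is relevant here because the factors under test bear on continued participation. One is a weekly call of up to 60 minutes against on-demand contact only. The other is a reward that grows with sustained participation against a flat one. The reasons for leaving could therefore differ between levels, although the article gives no figure for this. At stake is a possible small to moderate bias in the main effects used to choose components, and in any case a little precision.

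**Working it through.** **1. Reproduce the plan's own figure.** Inputs from Sample Size: 160 completers, two-sided 5%, 80% power, and correlation 0.6 ("we assume a conservative correlation of 0.6 between the baseline covariate and outcome"). Allocation is 1:1:1:1, so each factor level has 80 completers.

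- Residual SD after baseline adjustment: √(1 − 0.6²) = 0.8.
- SE of a main effect: 0.8 × √(2/80) = 0.1265.
- Detectable difference: (1.960 + 0.842) × 0.1265 = 0.354, or 0.357 with the t distribution.

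The stated value is "of 0.36 for the main effect or 0.18 in terms of the standardized regression coefficient", so it is reproduced. This calculation uses baseline and 6 months only, so adding the 3-month visit to the model does not invalidate it.

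**2. Precision lost by leaving out 3 months.** Assumptions not in the documents: baseline to 3-month correlation 0.6; 3-to-6-month correlation r = 0.7 (range 0.6 to 0.8); half of the attrition after month 3 (up to all of it); random dropout.

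- Partial correlation of the 3- and 6-month scores given baseline: (r − 0.36)/0.64. At r = 0.7 this is 0.531, squared 0.282.
- With half of the attrition late, each level has 90 scores at 3 months and 80 at 6 months. Variance ratio, three visits to two: 1 − 0.282 × (1 − 80/90) = 0.969.
- SE: 0.1265 × √0.969 = 0.1245. Gain: 3% of variance, or 160 × (1/0.969 − 1) ≈ 5 completers.
- Extremes: r = 0.6 with half late gives 1 − 0.141 × (1/9) = 0.984. r = 0.8 with all late gives 1 − 0.473 × 0.2 = 0.905.

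The gain therefore runs from about 2% to 10% of variance, and the achievable detectable difference moves from 0.354 to between 0.352 and 0.337.

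**3. Bias when dropout depends on the 3-month score.** This was simulated with correlations 0.6, 0.6 and 0.7, 20% total attrition in each factor level, and a true effect of 0.36 at 6 months and 0.18 at 3 months. Losses before month 3 were random. Later dropout was logistic in the 3-month score, with slope 0.5 to 1.5 per SD. The two-visit analysis regresses the 6-month score on factor and baseline. The three-visit analysis is maximum likelihood using the 3-month score as well.

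| Dropout after month 3 | Share of attrition after month 3 | Two-visit bias (SD) | Three-visit bias |
|---|---|---|---|
| Depends on score in one level, random in the other | half | about 0.02 to 0.05 (6% to 14% of 0.36) | near zero |
| Depends on score in one level, random in the other | all | about 0.03 to 0.08 (8% to 22% of 0.36) | near zero |
| Same dependence in both levels | half or all | near zero | near zero |

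Against the SE of 0.1265, the half-late bias is 0.16 to 0.40 SE and the all-late bias 0.24 to 0.63 SE. If those who score low leave, the level with score-dependent dropout looks better than it is. A rerun with one million participants per level gave the same ranges.

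**The case against.** **The parenthesis may name the contrast, not the data entered.** Statistical Methods opens by referring to several time points per participant, uses baseline as the reference cell, and calls 6 months the primary end point. A three-visit model with a 6-month contrast fits those words. This stands as an ambiguity, and it is why confidence is moderate. A reader might infer that the plan excludes the 3-month data, but it never says so. Equally, baseline and 6 months are already several time points, the pre-post wording points to two occasions, and no sentence brings the 3-month score in.

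**The missing-data plan is wider than the mixed model.** It includes multiple imputation and sensitivity analyses, either of which could use the 3-month score. That is true, so it would be wrong to read the plan as resting on the two-visit model alone. But neither is said to use that score, and a sensitivity analysis does not change the primary estimate.

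**Model detail belongs in the analysis plan.** Covariance structure and visit lists usually do, and their absence from a journal article is no fault. Here, however, the article names the time points for the primary model, and that list leaves out a planned visit.

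**The harm is conditional.** A reader might infer that any dropout related to the 3-month score biases the result. It does not: equal dependence in both levels leaves the contrast essentially unbiased. Nor do the documents show that dropout will differ. All participants receive the tracker, the platform and points, and those without scheduled calls can still reach a coach. The near-zero three-visit bias also holds only because simulated late dropout depends on the 3-month score and nothing later. The trial describes itself as exploratory, which limits severity further.

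**Conclusion.** The point holds in a limited form. As written, the primary model names two of the three planned occasions, and the 3-month SF-36E score has no stated use in the primary, imputation or sensitivity analyses. If that is how the model is fitted, the missing-at-random assumption is stronger than the planned data require.

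Only the small loss of precision applies when dropout is random or follows the 3-month score alike in both levels. The bias figures need dropout to follow that score differently between factor levels, and the larger range also needs every loss to come after the 3-month survey. Those conditions, the 3-month correlations and the slopes are assumptions. The documents support neither a prediction that this bias will occur nor a claim that the 3-month scores are the most informative dropout data. Participants lost before month 3 are not helped either way.

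This is a free improvement rather than a flaw that endangers the trial.

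**What to change.** State in Statistical Methods, and carry into the analysis plan, that the primary mixed model includes SF-36E at baseline, 3 and 6 months, with time as a categorical variable and an unstructured covariance matrix. Keep the component-by-time contrast at 6 months as the primary test and report the 3-month contrast as secondary. If three visits were always intended, the same sentence settles the ambiguity. It would also help to say that the 3-month score enters any multiple imputation and the sensitivity analyses.

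**Cost.** No extra data are needed, since the 3-month survey is already scheduled. The sample size of 200, the stated detectable difference of 0.36 and the primary end point do not change. For the full 2 × 2 model, the fixed effects rise from 4 × 2 = 8 to 4 × 3 = 12 and the covariance parameters from 3 to 6. That is seven more parameters, which 200 participants can support.
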